### Patient and public involvement

A patient carer and public involvement (PCPI) committee of five stroke survivors and two family members provides oversight into study procedures, study materials review, patient recruitment and support site set-up and training of healthcare professionals. The PCPI committee meets quarterly for the duration of the study. Prior to finalising the study design, the PCPI committee selected the candidate primary outcome measures, finalised participant-facing materials and design of fidelity scoring materials.

### Setting

The study will take place in England, UK, including stroke services that span the full care pathway from acute hospitalisation to 6-month review (see table 2 for details on eligible sites).

**Table 2 T2:** Inclusion and exclusion criteria of study participants

Sites	Patients who had a stroke	Carers	Healthcare professionals
Inclusion criteria			
Existing 6-month review offered to all patients who had a stroke within the service	Aged 18 years or older	Aged 18 years or older	Currently working within eligible stroke pathway NHS sites
Existing early supported discharge stroke service within NHS England	Within 4 weeks of confirmed clinical diagnosis of stroke (first ever or recurrent)	Cohabiting with stroke survivor	Currently deliver stroke reviews within eligible stroke pathway NHS sites
Capacity for research activity within the clinical team (ie, capacity for recruitment and to conduct enhanced reviews)	Sufficient English fluency	Able and willing to provide informed consent	Are able and willing to provide informed consent
	Ability to concentrate for 10 min, as judged by the clinical team		
	Ability to provide informed consent or favourable consultee advice for adults lacking capacity to consent		
Exclusion criteria			
		They are a paid or professional carer	

NHS, National Health Service.

### Participants

Patients who had a stroke, carers and healthcare professionals will be recruited. For patients who had a stroke, intentionally broad inclusion criteria (table 2) are used to ensure representativeness of real-world stroke clinical settings. Each stroke pathway will be responsible for the identification and recruitment of patients who had a stroke and carer participants and the delivery of ENRICH reviews.

Recruitment will occur following site initiation and training. Patients who had a stroke will be screened for eligibility within recruited sites and approached for participation by multidisciplinary team members. Given the waiver of consent for intervention delivery, recruited stroke participants will be invited to provide informed consent to provide outcome data collection and an optional semi-structured interview (see Outcomes for further details). Patients who had a stroke will be asked to optionally nominate a carer who the multidisciplinary team could approach for participation; not having a carer or not wishing a carer to take part will not preclude participation. Nominated carers will then be approached by the multidisciplinary team to take part and provide informed consent.

Clinical leads at each recruited site will identify healthcare professionals who meet study eligibility criteria, and will be approached following site initiation about participation. All study data collected will be held confidential and only accessible by those in the research team, with data made fully anonymised past study end.

### Healthcare professional training

The ENRICH intervention is intended to be a Level 2 psychological care intervention, in line with guidelines on providing matched care to stroke survivors,^19^ that can be provided by any member of a multidisciplinary team. Healthcare professionals at recruited stroke services are provided with 4 hours of training (in person or remotely via videoconferencing offered) covering an overview of the ENRICH study purpose and intervention structure, practical use of the ENRICH materials (eg, assessments, ENRICH patient workbook) and role play activities to familiarise themselves with implementation of ENRICH reviews.

### ENRICH Intervention

The ENRICH intervention provides stroke survivors with structured psychological reviews and 1, 3 and 6 months post-stroke, aiming to extend standard UK stroke reviews delivered at 6 months post-stroke only. In accordance with our co-production work^14^ ENRICH reviews comprise screening of psychological outcomes using standardised assessments of objective (Oxford Cognitive Screen; OCS^22^) and subjective (Checklist for Cognitive, Emotional and Behavioural Consequences following Stroke; CLCE^23^), mood (Patient Health Questionnaire-9; PHQ-9^24^), anxiety (Generalised Anxiety Disorder-7; GAD-7^25^) and fatigue (Fatigue Severity Scale; FSS).^26^ ENRICH reviews include communicating screening results from these measures and their implications to patients who had a stroke, and psychoeducation and self-management about their specific psychological changes. Where the stroke survivor views it to be beneficial, family members of stroke survivors are also invited to attend ENRICH reviews and complete a measure of subjective cognition of the stroke survivor to contribute to the review process. These elements are scaffolded using a co-designed ENRICH workbook, meant to serve as a communication tool and record of screening outcomes and information relevant to the patients who had a stroke. In addition to these specific factors, the co-production of ENRICH highlighted that reviews should also incorporate non-specific factors in terms of how each ENRICH component is implemented. ENRICH reviews should therefore include personalisation of reviews to the patients who had a stroke’s needs and circumstances, use accessible language and explaining any jargon terms, foster hope and optimism in the patients who had stroke and use compassion and sensitivity throughout the reviews. ENRICH reviews are designed to be delivered by clinicians providing Level 2 care in stroke services, including (but not limited to) assistant psychologists, occupational therapists, therapy assistants and speech language therapists.

In our single-arm multicentre feasibility study design, all patients who had a stroke in the site can receive ENRICH. We aim for all consenting and those with favourable consultee advice to receive ENRICH reviews. Participants will not be required to discontinue any ongoing care while receiving ENRICH.

### Participant Timeline

Stroke participant demographic data will be collected prior to the first ENRICH review at baseline (T1). Outcome data will be collected either via post, live via telephone/videoconferencing or using online surveys following completion of the final enhanced review at 6 months after stroke (T2; see table 3 for overview). Candidate outcomes were not collected at baseline as self-report assessments of quality of life were viewed not to be representative at time post-stroke of high emotional distress.

**Table 3 T3:** Overview of patients who had a stroke study outcome measures and additional data

	Baseline (T1)	Post-ENRICH assessment (T2)
Demographic information	✔	
Secondary outcome measures—candidate primary outcome measures for a future trial		
Quality of Life Instrument after Brain Injury		✔
WHO-Quality of Life Brief		✔
Process measures		
Patient Health Questionnaire-9		✔
Generalised Anxiety Disorder-7		✔
Modified Rankin Scale		✔
EQ-5D-5L		✔
Health Economics Questionnaire		✔
Additional data collection		
Custom post-study survey		✔
Semi-structured interview (~30% of participants)		✔

ENRICH, ENhanced Reviews of PsychologIcal Changes; EQ-5D-5L, EuroQol-5D-5Levels.

### Quantitative Outcome Measures

As family members/carers and healthcare professionals will only provide qualitative research data through a semi-structured interview and custom survey data, the below outcome measures will be completed by patients who had a stroke consenting to research data collection only.

### Primary Outcome

Given the study aims, the primary outcome measures for this study are feasibility measured by descriptive statistics on recruitment, attendance and completion of study measures over the course of the study.

### Key Secondary Outcome Measures—Candidate Primary Outcome Measures for a Future Trial

In order to ultimately evaluate whether ENRICH is an effective intervention, a future effectiveness trial should evaluate a meaningful outcome. In collaboration with our PCPI group, the candidate primary outcome for future evaluation was determined to be quality of life. In the present study, these are key secondary outcome measures relative to the primary outcome measures assessing feasibility above. Following PCPI discussions, we selected two potential candidate primary outcome measures as below, for which we aimed to determine acceptability and completion rates in the present study.

The Quality of Life Instrument after Brain Injury (QOLIBRI) is a 37-item self-report measure of health-related quality of life following brain injury. The measure is designed to measure aspects of health-related quality of life associated specifically with brain injury such as thinking abilities, emotions, functioning and social activities and the degree to which individuals are bothered by them. The QOLIBRI was specifically developed and validated for brain injury populations.^27^

The WHO-Quality of Life-Brief (WHO-QOL-BREF) is a 39-item patient-reported outcome measure designed to capture quality of life across physical, psychological and environmental domains and capture how quality of life has been affected by disability. The WHO-QOL-BREF has been validated for patient use across multiple patient populations including stroke.^28^

### Process Measures

Process measures were selected to capture theoretically relevant constructs that may moderate responses to the ENRICH intervention or shift as a result of the intervention, as well as provide descriptive information about improvement more generally. This includes depressive symptoms (PHQ-9), anxiety symptoms (GAD-7) and functional ability (modified Rankin Scale^29^).

### Additional Quantitative Data Collection

We will additionally collect scores on the OCS, CLCE, PHQ-9, GAD-7 and FSS completed with patients who had a stroke during ENRICH reviews. These will be used to describe the recruited cohort.

### Health Economic Evaluation

Alongside candidate primary and secondary outcome measures, stroke participants will complete measures of healthcare resource use and quality of life including the EuroQol-5D-5Levels and the Health Economics Questionnaire (HEQ) is a 5-item customised measure of health resource use post-stroke, developed with a health economist and the PCPI committee. Participants are asked to report on amount and type of unpaid care received, medication use, re-admission to hospitals, health service use (eg, General Practitioner use) and employment status.

### Quantitative Data for Uncertainties in Study Design

With regards to study design, quantitative data on number of sites meeting initial site eligibility and numbers of expressions of interest will be collected. Per site, participant eligibility rates (defined as percentage of patients per site meeting study eligibility criteria), recruitment rates (total number of patients recruited per month across both informed and consultee advised consent), intervention completion (total number of ENRICH reviews received) and outcome completion rates for patients who had a stroke, carers (T2 assessment completion rates) and healthcare professionals (interview completion) will be collected.

### Quantitative Data for Uncertainties in Intervention Delivery

Our quantitative aims with regards to the delivery of the intervention are to investigate the numbers of trained clinicians delivering ENRICH reviews, proportions of recruited patients receiving ENRICH reviews and ratings of perceived helpfulness and usefulness (assessed using a custom Likert scale from 1 to 5) of ENRICH from healthcare professionals, patients who had a stroke and carers.

### Quantitative Data for Uncertainties in Research Data Collection

We aim to assess completion rates of candidate outcome measures (ie, total proportion of participants completing each outcome measure) at T2 to inform acceptability. We will additionally assess total proportion of patients consenting to audio recordings for fidelity. Through the HEQ, we will additionally assess number of healthcare services used to describe usual care and inform the future control arm.

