The ENhanced Reviews of PsychologIcal Changes (ENRICH) intervention was developed iteratively and rigorously following the Medical Research Council (MRC) framework for complex intervention development,^13^ detailed in Hobden and Demeyere.^14^ The final ENRICH intervention consists of an iterative (1, 3 and 6 months) monitoring and management programme for post-stroke psychological changes using ENRICH reviews. Each ENRICH review provides assessment, feedback and personalised psychoeducation on domain-specific cognition, mood and fatigue, with self-management strategies and onward referral to specialist services as indicated. The ENRICH training and reviews also emphasise non-specific elements of psychological care, such as personalisation, explaining jargon, fostering hope and optimism and using compassion and sensitivity throughout the reviews. The ENRICH intervention provides a holistic framework for enhancing the psychological care pathway for stroke survivors.

In this study, we aim to determine the feasibility, acceptability and fidelity of ENRICH reviews delivered in clinical stroke services by a range of healthcare professionals to inform a potential future pragmatic randomised cluster trial.

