#### Our specific aims were to evaluate

Acceptability of ENRICH to NHS healthcare professionals, patients who had a stroke and family members, and of quality of life and health economic outcome measures.Feasibility of site recruitment, participant recruitment and retention rates, most effective methods of consent and delivery of ENRICH reviews.Fidelity of the ENRICH intervention when delivered by NHS healthcare professionals.

All recruited sites will only be required to implement the ENRICH intervention (ie, no control site). Given data in acute and subacute stroke populations on recruiting and conducting complex interventions at the cluster level using controlled designs,^15^,^17^ we have adopted a design to capture the most relevant data and prioritise evaluation of ENRICH intervention training and delivery, to inform progression to a pragmatic effectiveness trial. We include a waiver of consent for the ENRICH intervention delivery only in accordance with the Ottawa statement on Ethical Design and Conduct of Cluster Randomised Trials,^18^ given that the intervention is arguably in line with minimum stroke care standards and is unlikely to cause harm. The waiver of consent covers the delivery of the full ENRICH intervention delivered at 1, 3 and 6 months post-stroke, including conducting the assessments, communicating screening results and self-management of psychological changes (see ENRICH intervention below for further specifics). A single-arm multicentre feasibility study design with a waiver of consent for intervention delivery was selected because (1) ENRICH was designed to be implemented for all patients who had a stroke in a service as a standard of psychological care; (2) we aim to evaluate the ENRICH intervention as a service change for all, rather than an intervention for only a specific subset of patients who had a stroke, and (3) there was deemed a potential for contamination within a service where ENRICH-trained healthcare professionals typically jointly discuss patients who had a stroke care, thereby also limiting the potential for evaluation within an individually randomised controlled trial.

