### Uncertainties in Research Data Collection

It was unknown what the estimated completion rates and attrition would be for completion of the outcome measures, as well as uncertainty around which of two candidate quality of life outcome measures to use and whether health economic data could be captured adequately (see Outcomes for details on study measures). Further, it was unknown whether participants would find collecting fidelity data (see Fidelity section below) acceptable.

Taken together, we aimed to investigate acceptability and feasibility of the intervention delivery, as well as design feasibility of a future cluster design including waiver of consent for delivery of the ENRICH intervention. A summary of our key uncertainties and associated data we aim to collect is in table 1. Our qualitative aims with regards to delivering the intervention were to explore the acceptability of the ENRICH training by healthcare professionals and the ENRICH reviews by patients who had a stroke, carers and healthcare professionals through surveys and interviews. In addition, we will examine the fidelity to non-specific factors through audio recordings of reviews and explore barriers and facilitators of the implementation of the ENRICH reviews in clinical stroke services. With regards to study design, we aim to explore participants’ views on study procedures, materials and outcome measures, alongside understanding standard clinical care.

**Table 1 T1:** Summary of key uncertainties and associated data to be collected

Evaluation domain	Study component	Data source	Key uncertainty	Associated quantitative data	Associated qualitative data
**Feasibility**	**Study design**	Sites	Can we recruit sites?	Number of eligible sites expressing interest	
			How many patients receive ENRICH with waiver of consent?	Total number of reviews delivered	
			What is the standard of care?	Number of non-ENRICH clinical contacts	Descriptions of standard care across each recruited site
		Healthcare professionals	What is the most effective consent method?	Proportion consented by clinician role	
			Can we recruit and retain sufficient numbers?	Recruitment and attrition rates	
		Patients who had a stroke	Can we recruit and retain sufficient numbers?	Recruitment and attrition rates	
			Can we recruit a diverse sample?	Patient demographics vs national audit data	
			How many ENRICH reviews do participants receive?	ENRICH review completion rates	Reasons for non-completion

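### Service use measured only after ENRICH, in a single-arm study, is to be reported as usual care for the future control arm, although it can include use that ENRICH itself prompted

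*Protocol article*

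**What the plan says.** Under Quantitative Data for Uncertainties in Research Data Collection, the article gives the HEQ count a purpose beyond testing whether it can be collected: "Through the HEQ, we will additionally assess number of healthcare services used to describe usual care and inform the future control arm". Table 1 lists a second quantity, with sites as the data source, against the question of what standard care is: "Number of non-ENRICH clinical contacts". Beside it stand qualitative descriptions of standard care at each site. The section Qualitative Data for Uncertainties in Research Data Collection adds site surveys on usual care, also meant to inform the control arm.

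The setting in which these are measured is stated elsewhere:

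- Control sites (Our specific aims were to evaluate): "All recruited sites will only be required to implement the ENRICH intervention (ie, no control site".
- Exposure (ENRICH Intervention): "We aim for all consenting and those with favourable consultee advice to receive ENRICH reviews".
- Respondents (Quantitative Outcome Measures): "the below outcome measures will be completed by patients who had a stroke consenting to research data collection only".
- Timing (Participant Timeline): outcome data are collected "following completion of the final enhanced review at 6 months after stroke (T2; see table 3 for overview". Table 3 ticks the HEQ at T2 only.
- Content of a review (Introduction): assessment, feedback and psychoeducation, "with self-management strategies and onward referral to specialist services as indicated".
- Relation to existing care (ENRICH Intervention): "aiming to extend standard UK stroke reviews delivered at 6 months post-stroke only". Participants need not stop other care.

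**The concern.** Usual care for a future control arm means care in a service that does not deliver ENRICH. The people who answer the HEQ are patients of services that do deliver it, asked after the last review. One component of ENRICH is referral to other services, and use of health services is part of what the HEQ records. The count therefore describes care alongside ENRICH and partly resulting from it, yet it is labelled as the comparator.

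The article names the minimum care standard for a future control arm as a key uncertainty (Uncertainties in Study Design). It also says that the present pathway does not routinely provide care for psychological changes after stroke (Introduction). Referrals for those changes act on exactly that gap. If the use they generate is read as usual care, the team planning the cluster trial could take the control arm to be better served than it is.

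**Working it through.** The plan states no usual-care figure, so there is none to reproduce. The check is whether any planned quantity measures care without ENRICH.

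**1. The HEQ count.** There is no control site, no baseline HEQ and no unexposed respondent by design. Referrals made at the 1-month and 3-month reviews have 6 − 1 = 5 and 6 − 3 = 3 months to turn into service use before T2. As described, the HEQ covers unpaid care, medication, re-admission, health service use and employment. Nothing in that description separates use that followed an ENRICH referral. The items themselves are not shown.

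**2. Patients who miss reviews.** They are not a clean usual-care group either. The article's own reason for not randomising individuals is contamination, because trained staff in a service discuss patients jointly.

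**3. The Table 1 count.** Leaving out ENRICH visits does not leave out the specialist contacts that those visits lead to. A second effect is possible in this count only. Table 2 requires sites already to offer a 6-month review. Where ENRICH is delivered as part of that visit, the visit may be classed as ENRICH and drop out of the count.

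**4. Size, by assumption only.** For the Table 1 count, let r be the share of patients who have a referral that would not have been made without ENRICH, c the contacts per such referral, and s the standard reviews absorbed (0 or 1). The shift in mean contacts per patient is r × c − s. The article gives none of these. Taking r from 0 to 0.5 and c from 1 to 4:

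| r | c | s | shift |
|---|---|---|---|
| 0 | any | 1 | −1.0 |
| 0.1 | 1 | 0 | +0.1 |
| 0.3 | 4 | 1 | 0.3 × 4 − 1 = +0.2 |
| 0.5 | 1 | 1 | 0.5 × 1 − 1 = −0.5 |
| 0.5 | 4 | 0 | 0.5 × 4 = +2.0 |

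The range, −1.0 to +2.0, includes zero and both signs. It shows only that the direction is open. It does not carry over to the HEQ statement, which speaks of the number of services used, not contacts, and which is not described as leaving out ENRICH visits.

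**5. Sample size does not help.** Up to 80 patients less 25% attrition gives 80 × 0.75 = 60 completers. The 95% confidence half-width for a mean is then 1.96/√60 = 0.25 SD, or 1.96/√80 = 0.22 SD with all 80. Both cover sampling error only and leave the shift untouched.

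**The case against.** The strongest reply is that the HEQ is not the main source on usual care. What a control arm would look like is mostly a question of what services provide, and the site surveys and site descriptions address that directly. Table 1 uses the HEQ for completion rates, all quantitative reporting is descriptive, and no progression criterion in Table 4 uses an HEQ count. That stands, and it limits the consequence. It does not make the stated use of the count sound.

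Three more objections stand in part. Some ENRICH referrals would have been made anyway, so not every one adds to usual care. Referrals at the 6-month review have little time to show by T2, although those at 1 and 3 months do. Full exposure is an aim: the green criterion needs only half of participants to complete more than one review. Partial delivery dilutes the effect without removing it.

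A reader might go further and infer that ENRICH takes over the standard 6-month review, so that this review is lost from every patient's count. The article does not say so. It speaks of extending standard reviews, lets ongoing care continue, and notes that many existing reviews deal mainly with secondary prevention or physical recovery. Absorption is possible but undocumented. The review is in any case a site eligibility condition, so it is a known feature of usual care.

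A reader might also infer that the future trial's contrast between arms and its control-arm cost will be wrong. No passage says that these counts will set either.

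**Conclusion.** The point holds in a limited form. As planned, the HEQ count is service use under ENRICH and cannot be read as usual care. Table 1's non-ENRICH contact count does not cure this, and it may have an omission of its own. The conclusion rests on four stated facts: a single arm with no control site, intended exposure of all participants, HEQ collection at T2 only, and onward referral as part of ENRICH. It needs no assumed figure. The size and direction of the bias cannot be settled from the article, and the range shown above is illustration only.

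The feasibility, acceptability and fidelity outcomes are unaffected. What is affected is one quantitative input to a named uncertainty for the next trial. The change is worth making now, because a later analysis cannot identify referral-prompted use unless referrals are recorded during the study.

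**What to change.** 1. Under Quantitative Data for Uncertainties in Research Data Collection, report the HEQ result as *service use under ENRICH* and drop the statement that it describes usual care.
2. Base the control-arm description on the site surveys already planned, and word them to ask about care before ENRICH started. Where sites can supply it, add an anonymised aggregate count of psychological contacts and referrals for that period.
3. Add one field to the existing per-review fidelity checklist: whether an onward referral was made, and to which service. Service use can then be reported with ENRICH-prompted referrals shown separately.

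Do not construct a usual-care count by removing ENRICH-initiated contacts and adding back a 6-month review. Removal would also discard referrals that usual care would have made, and adding back would double-count the review wherever it took place separately.

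The cost is a wording change, one checklist field and, optionally, one aggregate return per site. No visit, patient or arm is added.
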